#### Data Analysis

Content analysis will be performed on responses to open-ended questions to reveal contexts of use, usability issues, features most and least liked, facilitators and barriers, any anticipated negative effects, usefulness of the app for homework completion, and suggestions for improvement. Responses will be summarized in narrative form and frequencies of each category will be calculated. Descriptive statistics will be performed on the Likert-type ratings to measure central tendency (mode) and variability (frequencies). The cognitive skills assessment will yield clustering profiles outlining areas of strength and challenge as compared with others, permitting an exploratory qualitative analysis of associations between cognitive profiles and the usability evaluation data. The results of the study will be used to determine whether the app is usable and safe to use in the context of treatment, and thus is ready for a clinical trial of its effectiveness and acceptability in a treatment context, and to further improve the app before proceeding.

### Phase 3: Evaluation of Effectiveness

The purpose of Phase 3 is to evaluate the impact of the app on homework completion. We hypothesize that participants in the app group will show greater homework adherence than those in the no-app group. To test the hypothesis, a pragmatic clinical trial will be conducted at the same 5 clinic sites as in Phase 2. CBT is well supported by randomized controlled trials of its efficacy when delivered in different ways, including computerized formats as described above. Therefore, the purpose of this phase is not to determine CBT efficacy, but rather to provide evidence that homework (ie, the practice of CBT skills and strategies) can be effectively delivered in a mobile format [94]. Thus, the main objective is to assess the impact of the app on homework completion compared with CBT treatment-as-usual (ie, paper-based homework delivery). We will also obtain end user evaluations of the app’s usability in the context of treatment. Finally, we will also conduct exploratory analyses to assess the impact of the app on symptom improvement and cost-effectiveness, and to examine associations between cognitive profiles and homework completion as well as user experience.

#### Study Design

We will conduct a multisite, randomized controlled pragmatic clinical trial in routine clinical settings to test the app’s effectiveness under real-world conditions in order to enhance external validity and ensure successful implementation without sacrificing scientific rigor. A pragmatic clinical trial also suits the nature of mHealth technologies, which require ongoing improvement and are subject to rapid technological change [95-97]. After pretreatment assessment, participants will be randomly assigned to receive a manualized CBT treatment either with app support (app group) or without it (no-app group). Youth assigned to CBT with the app will receive CBT treatment for 12 weeks with the app included (app group). They and their therapists will be shown how to use the app. Youth assigned to receive CBT treatment for 12 weeks with paper-based homework will be in an active control condition (no-app group). Both groups will be in treatment for 12 weeks, the typical duration of CBT. However, therapists in both the app and no-app groups will be able to provide additional sessions should they deem it clinically relevant. Duration of CBT will be recorded and group differences will be analyzed. Following the pretreatment assessment and exclusions, participants providing informed consent will be randomly assigned to treatment group. Random assignment will be done at each test site separately by the site coordinator. At each site, half the participants will be assigned to each group in order to control for site-specific variables (eg, type of CBT delivered, professional background of therapist). To assess the app’s effectiveness both immediately and over time, assessments will be done at the end of the 12-week treatment (posttreatment) and again after 6 months (follow-up 1) and 12 months (follow-up 2). At each time-point, participants will receive a CAD$30 gift card as an honorarium.

#### Sample Size and Power

Given the low rates of homework completion in research to date, we expect that the app will have at least a moderate effect on homework completion compared with the no-app group [28,35,36]. A power calculation, based on a comparison between 2 groups (app vs no-app) across 4 occasions (pre, post, follow-up 1, follow-up 2) for a single measure, indicates that a sample size of 35 for each group would provide power of 0.84 to detect a moderate effect size for homework completion at α = .05. To allow for dropouts [98], we will recruit 100 youth between 12 and 18 years of age (10 per group at each site). As noted earlier, treatment dropout rates can be substantial and adherence to homework is often quite low. This has been taken into account in calculating the sample size. The expectation is that compliance will be greater for the app than the no-app group. Based on previous research with youth [98], we expect a 10% rate of attrition at each of the 2 follow-ups.

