#### Measures

At pretreatment, as in Phase 2, we will assess (1) demographic characteristics and comfort with technology to characterize the sample, and (2) cognitive skills to examine associations between cognitive profiles and homework completion as well as user experience.

During treatment, homework completion will be assessed weekly. The quantity (amount) as well as the quality (appropriateness) of homework will be assessed, based on evidence that they both relate to treatment outcome [99]. Multiple sources of homework information (adolescent, therapist, data logged by the app) will be obtained to address potential differences between sources [99,100]. Adolescents will assess the quantity and quality of their homework upon arriving at the session, by rating on a 5-point scale how much of it was completed and how well it was done, using 2 items from the Homework Rating Scale II [101], an internally consistent measure of homework quantity and quality developed for use with adults [102]. The 2 items have not previously been tested with adolescents and will be pilot-tested in this study. Two additional measures of homework quantity will be obtained by asking adolescents to estimate the number of days and the number of hours they spent doing homework [103]. Therapists will assess homework completion following the session. They will assess homework quantity by rating the proportion of assigned homework that was completed (from 0% to 100%), a method used in previous research [36,103]. They will rate the quality of the work on a 6-point scale [104], using criteria specified for each assignment; this measure has been found to predict treatment outcome [103]. A third source of information about homework quantity will be obtained in the app group from data logged by the app: the proportion of the task completed, the time spent on the task, and the number of visits to the assignment page.

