##### Homework Completion

Effects of the app on homework completion will be analyzed separately for homework quantity and quality. Psychometric properties of the measures will be examined and correlations will be computed to examine congruence between adolescent and therapist sources of information. If warranted, aggregate scores will be computed; otherwise, separate analyses will be done using different measures. To test the hypothesis that the quantity and quality of homework will be greater in the app compared with the no-app group, we will test group differences in quantity and quality scores. We will also explore timing effects, given evidence suggesting that homework completion varies over time and may decrease over the course of treatment [36]. Scores for the first 4, middle 4, and final 3 weeks of homework will be averaged, creating 3 assessment points, and a mixed-model repeated measures multivariate analysis of the variance will be performed with the between factor of group (app vs no-app), the within factor of time (early, middle, late), and the 2-way interaction of group × time.

Exploratory analyses will also be performed. Subgroup analyses will explore differences in the app’s impact on homework completion as a function of test site and gender. Correlations will explore relations between cognitive profiles and homework completion. For the app group, psychiatric and cognitive assessment data will be aggregated and advanced analytics will be performed to examine predictive relations between patient attributes (anxiety, depression, cognitive profile) and the quantity and quality of homework completion. These analyses will include homework completion data logged by the app (proportion of the task completed, the time spent on the task, and the number of visits to the assignment page).

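### The 0.84 power for homework completion is calculated on four occasions (pre, post, two follow-ups), but homework is measured only during treatment

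*Protocol article*

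**What the plan says.** Under Sample Size and Power, the protocol article says that "a sample size of 35 for each group would provide power of 0.84 to detect a moderate effect size for homework completion", with alpha .05. The calculation is described as "based on a comparison between 2 groups (app vs no-app) across 4 occasions (pre, post, follow-up 1, follow-up 2) for a single measure". The expected effect is "at least a moderate effect on homework completion compared with the no-app group"; no numeric effect size and no correlation between occasions is given. Recruitment is set at 100 (50 per group) to allow for dropout. The section expects 10% attrition at each of the two follow-ups and says that treatment dropout was also considered.

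The homework outcome is described elsewhere:

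- Measures: "During treatment, homework completion will be assessed weekly". The measures listed for pre, post and each follow-up are treatment outcomes: symptoms, diagnosis, maladaptive cognitions and quality of life. Homework is not on that list.
- Homework Completion: the hypothesis is tested as group differences in quantity and quality scores. Timing is then explored: "Scores for the first 4, middle 4, and final 3 weeks of homework will be averaged, creating 3 assessment points", in a group by time model with early, middle and late levels.
- Treatment Outcomes: the exploratory symptom analysis is the one whose time factor is pre, post, follow-up 1 and follow-up 2.

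**The concern.** CBT homework is set between therapy sessions. The plan provides no homework score before treatment starts or at 6 and 12 months after it ends. Three of the four occasions in the power sentence therefore carry no homework data, and post is an assessment visit at which homework is not listed either. The outcome named in the sentence and the design named in the sentence do not belong together.

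This matters because greater homework adherence in the app group is the only hypothesis stated for Phase 3, and this sentence is the only quantitative support for the sample size. A null homework result would be judged against 0.84, a figure worked out for a different layout.

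**Working it through.** **Inputs from the protocol article.** 35 per group (N = 70); alpha .05; four occasions in the power sentence; three in-treatment means in the homework analysis; 100 recruited, allocated equally.

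**Assumptions, because the article gives no figures.** A moderate effect is f = 0.25, that is d = 0.5 in the SD of a single occasion or period mean. The test is two-sided. All pairs of occasions share one correlation ρ (compound symmetry).

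**Formula.** For the group effect averaged over m occasions, power comes from the noncentral F distribution with 1 and N − 2 degrees of freedom and noncentrality

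λ = N × f² × m / (1 + (m − 1)ρ).

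**Step 1: reproduce the stated 0.84.** N × f² = 70 × 0.0625 = 4.375. With m = 4 and ρ = 0.316, λ = 17.5 / 1.948 = 8.98 and power is 0.840. At ρ = 0.3 it is 0.849. The figure can thus be reproduced as a four-occasion calculation, given a correlation near 0.32.

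**Step 2: put in the occasions at which homework is measured.** With m = 3 the numerator is 4.375 × 3 = 13.125.

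| ρ | 4 occasions, 35 per group | 3 periods, 35 per group | 3 periods, 40 per group | 3 periods, 50 per group |
|---|---|---|---|---|
| 0.3 | 0.849 | 0.806 | 0.856 | 0.924 |
| 0.316 | 0.840 | 0.798 | – | – |
| 0.5 | 0.742 | 0.714 | 0.772 | 0.858 |
| 0.7 | 0.649 | 0.635 | 0.695 | 0.790 |

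Two worked cells at ρ = 0.5: for 35 per group, λ = 13.125 / 2 = 6.56 and power is 0.714; for 50 per group, λ = 100 × 0.0625 × 3 / 2 = 9.375 and power is 0.858.

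With three periods, 0.84 is reached at 35 per group only if ρ is about 0.23 or lower, and at 50 per group if ρ is about 0.55 or lower.

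**Step 3: which correlations are plausible?** The article gives none. Averaging raises the correlation between periods: if weekly scores all correlate w, two 4-week means correlate 4w / (1 + 3w). For w = 0.2 this is 0.8 / 1.6 = 0.50; for w = 0.3 it is 1.2 / 1.9 = 0.63. A value of 0.23 or lower between period means would need weekly scores that are only weakly related.

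**Step 4: does the reading of the test matter?** If the stated power was meant for the group by time interaction, with λ = f²(N − 2)(m − 1), four occasions give 0.856 and three give 0.735, so the figure again falls. An interaction convention that scales f by the within-person variance gives 0.95 or more for four occasions and does not reproduce 0.84.

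**The case against.** The strongest reply is that 0.84 is reproducible and that the mismatch alone costs little: at a correlation of 0.316, going from four occasions to three lowers power from 0.84 to 0.80. The rest of the shortfall comes from a correlation that a journal article may leave to the full protocol. This stands. Its absence from the article is no fault in itself, and 0.5 and 0.7 are illustrative values, not the trial's own. What remains is that the occasions are stated, and they are not homework occasions.

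Three stronger readings are tempting, and the documents do not support them.

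- *The trial is underpowered.* It recruits 50 per group, and Data Analysis plans intent-to-treat analysis with missing values replaced. With all 100 analysed, power is 0.86 at a correlation of 0.5.
- *Power is only 0.54 if homework is tested on one overall mean.* That figure takes d = 0.5 in the SD of the overall mean. Under compound symmetry the group test on three period means is the test on their average: d = 0.5 per period at ρ = 0.5 is 0.5 / √(2/3) = 0.61 on the average, with the same power of 0.71. The 0.54 only redefines what moderate means. It does show why the scale of the effect must be stated.
- *The dropout allowance contradicts itself, since two 10% losses leave 100 × 0.9 × 0.9 = 81, not 70.* The section says that treatment dropout was also allowed for. A loss of about 14% during treatment would close the gap (70 / 81 = 0.864). That rate is a back-calculation and not in the article, but it shows there need be no contradiction.

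It is also fair to say that the three-period model is introduced as an exploration of timing, while the hypothesis itself is put as a group difference in scores. Either way the data are in-treatment scores, so the mismatch is the same.

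**Conclusion.** The power statement is wrong as written: it attaches 0.84 to homework completion over four occasions that match the exploratory symptom analysis and not the homework measurements. That conclusion needs no assumption.

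Its size does rest on assumptions: f = 0.25 per period, two-sided alpha 0.05, compound symmetry and the group effect as the test. On these, 35 per group gives 0.80 for the in-treatment comparison at the correlation that yields the stated 0.84, then 0.71 at 0.5 and 0.64 at 0.7. With 50 per group the figures are 0.86 and 0.79 at those last two correlations. The justification fails; the sample size of 100 may still be adequate, depending on the correlation and on how many participants leave during treatment.

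**What to change.** Replace the power sentence with power for the homework comparison that will be run, on the overall in-treatment mean or the three period means. State the numeric effect size, the SD it is scaled to and the assumed correlation. For example: *for f = 0.25 per period (d = 0.5 in the SD of a period mean) and two-sided alpha .05, 35 per group gives power of 0.71 at a between-period correlation of 0.5 (0.64 at 0.7); 50 per group gives 0.86 (0.79).* The sponsor should put in its own correlation if it has one.

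In the same paragraph, say that the 10% loss at each follow-up applies to the symptom outcomes and not to homework, and give separately the in-treatment dropout assumed for homework. That rate has to come from the sponsor.

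The cost is one rewritten paragraph and possibly a less favourable power figure. No extra participants are needed, and no outcome, visit or analysis changes.

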#### Recruitment

Recruitment will be the same as in Phase 2. In previous work in our clinics, consent rates have been 80% or higher. Interest in using the app is expected to be high. Typically, intake at the test sites is approximately 1 per week and the wait-list period is at least 12 weeks for noncrisis patients. Therefore, based on intake and consent rates and assuming sequential recruitment, we will recruit at a rate of 5 youth per week across the 5 sites, reaching an overall sample of 100 within 6 months. Posttreatment assessments would be completed at the end of treatment (ie, 3 months later), and the follow-ups 6 and 12 months thereafter. The same inclusion and exclusion criteria apply as in Phase 2.

#### Measures

At pretreatment, as in Phase 2, we will assess (1) demographic characteristics and comfort with technology to characterize the sample, and (2) cognitive skills to examine associations between cognitive profiles and homework completion as well as user experience.

During treatment, homework completion will be assessed weekly. The quantity (amount) as well as the quality (appropriateness) of homework will be assessed, based on evidence that they both relate to treatment outcome [99]. Multiple sources of homework information (adolescent, therapist, data logged by the app) will be obtained to address potential differences between sources [99,100]. Adolescents will assess the quantity and quality of their homework upon arriving at the session, by rating on a 5-point scale how much of it was completed and how well it was done, using 2 items from the Homework Rating Scale II [101], an internally consistent measure of homework quantity and quality developed for use with adults [102]. The 2 items have not previously been tested with adolescents and will be pilot-tested in this study. Two additional measures of homework quantity will be obtained by asking adolescents to estimate the number of days and the number of hours they spent doing homework [103]. Therapists will assess homework completion following the session. They will assess homework quantity by rating the proportion of assigned homework that was completed (from 0% to 100%), a method used in previous research [36,103]. They will rate the quality of the work on a 6-point scale [104], using criteria specified for each assignment; this measure has been found to predict treatment outcome [103]. A third source of information about homework quantity will be obtained in the app group from data logged by the app: the proportion of the task completed, the time spent on the task, and the number of visits to the assignment page.

At pre, post, and each follow-up, treatment outcomes will be assessed. Anxiety and depression will be assessed using the same instruments as in Phase 2: the Achenbach Scales, which assess general symptomatology as reflected in internalizing problems, and externalizing problems, which often co-occur with anxiety and depression [105], the MASC-2, the CDI-2, and the ADIS. Other outcomes also will be assessed. Maladaptive cognitions will be assessed using the Children’s Automatic Thoughts Scale [106], in which youth rate the frequency over the past week of a set of 40 self-statements describing negative thoughts about physical threats, social threats, personal failure, and hostile intent. Quality of life will be assessed by the Pediatric Quality of Life Inventory [107,108], in which youth rate 23 self-statements assessing physical, emotional, social, and school functioning.

At posttreatment, a usability evaluation will be conducted with the app group (youth and therapists) following completion of the posttreatment assessment, using the same protocol as in Phase 2. To examine differences in client satisfaction between the app and no-app groups, will be assessed posttreatment (following the usability evaluation in the app group) via the Client Satisfaction Questionnaire (CSQ [109,110]), an 8-item global measure of satisfaction with service comprised of statements phrased as questions to be answered on a 4-point scale ranging from 1 (poor) to 4 (excellent). The CSQ is a well-established measure with good psychometric properties [110] that has been used in numerous studies with diverse patient samples, including children and adolescents in CBT [111,112]. Treatment fidelity will be assessed by an integrity-to-protocol checklist [113], which therapists will complete after each session. The checklist yields a proportion score reflecting the rate of adherence to the CBT treatment manual. Finally, health economic cost data will be obtained to assess cost-effectiveness of the app. Cost data will consist of technology costs, including detailed micro costing of the app program (eg, program costs, smartphone-related costs, server costs, maintenance), and the cost of time and other resources needed to integrate the app into routine clinical practice by therapists and clinics.

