The usability evaluation by youth will be done via a short weekly interview conducted upon arrival at the therapy session. The interview will focus on the app’s usability for the assignment given at the end of the previous session. We will assess the efficiency of the app, via ratings of the app’s learnability (how easy to figure out and remember what to do), ease of use (the time and number of steps it takes to operate, need for technical support), and error tolerance (how free of error messages, app’s ability to prevent/recover from use errors). We will also assess satisfaction with the app, via subjective ratings of its learnability (access to the assignment, memory and understanding of the lesson, motivation to practice, coaching and suggestions, self-monitoring of symptoms and changes), usability (how easy it was to use), and likeability (of specific design features). In addition, open-ended questions will be asked about: (1) where, when, and how the app was used (to understand context of use), (2) problems using the app (to identify usability problems), and (3) how the app supported homework completion (to understand the usefulness of the app). The final evaluation interview will include additional items focusing on overall experiences and impressions of the app, ratings of the app’s overall efficiency (learnability, ease of use, error tolerance), and overall satisfaction with the app (usefulness, usability, likeability). Open-ended questions will be asked about features most and least liked, facilitators and barriers to use, any negative experiences associated with the app (eg, intrusion on privacy or fear of such an intrusion), how much the app supported learning (ratings of support for access to assignments, memory and understanding of lessons, motivation, coaching and suggestions, self-monitoring, review of homework), and any suggestions for improvement.

The usability evaluation by therapists will be done via an interview following the final session, through open-ended questions about the usefulness of the app for reviewing and troubleshooting homework, whether there were any negative effects of using the app, and any suggestions for improvement.

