If the analyses reveal significant group differences in treatment outcomes, additional exploratory analyses will be performed to aid interpretation of the data. To explore whether better homework completion (greater quantity and/or quality) or something unique about the mobile technology is most likely responsible for group differences in treatment outcomes, we will examine associations between homework completion and treatment outcomes separately for the 2 groups. Mobile devices may increase patient engagement and empowerment [1,117] and reduce concern about the perceived stigma associated with receiving treatment [118], resulting in beneficial effects on treatment that are independent of homework completion. Accordingly, regression analyses (ordinary least squares, logistic) would be performed to predict each of the dichotomous (diagnosis) and continuous (symptom severity) outcomes at posttreatment, follow-up 1, and follow-up 2 from measures of homework completion, controlling for the pretreatment value of the outcomes. A finding of group differences in the strength of associations between homework completion and treatment outcomes would suggest that an improvement in homework completion is not the only mediator of app effects on treatment outcome.

Finally, if treatment outcomes are better for the app compared with the no-app group, exploratory mediation analyses will be performed for the app group to assess whether homework completion (quantity, quality) affects treatment outcomes indirectly through support for learning (ratings of how much the app supports access to assignments, memory and understanding of lessons, motivation to practice, coaching and suggestions, self-monitoring of symptoms and changes, review of homework). To test for mediation, we will perform tests of indirect effects using a regression-based path-analytic approach [119,120].

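### The support-for-learning ratings used as mediator appear to be taken after the posttreatment outcome, so an indirect effect on that outcome cannot be read as mediation (minor, exploratory analysis)

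*Protocol article*

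**What the plan says.** Protocol article, Phase 3, Data Analysis, Treatment Outcomes (last paragraph): if outcomes are better with the app, "exploratory mediation analyses will be performed for the app group". Their stated aim is "to assess whether homework completion (quantity, quality) affects treatment outcomes indirectly through support for learning". The mediator is a set of six ratings of the app's support: access to assignments, memory and understanding, motivation, coaching, self-monitoring, and review of homework. Indirect effects are tested "using a regression-based path-analytic approach". The paragraph gives no outcome time point and no covariate.

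Protocol article, Phase 3, Measures: the timing is given in these words: "a usability evaluation will be conducted with the app group (youth and therapists) following completion of the posttreatment assessment". The instrument is carried over from the earlier phase, "using the same protocol as in Phase 2". Symptoms and diagnoses are assessed at pretreatment, posttreatment and both follow-ups. Homework is assessed weekly during treatment.

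Protocol article, Phase 2, Procedure: the final evaluation interview asks how far the app supported learning, with "ratings of support for access to assignments, memory and understanding of lessons, motivation, coaching and suggestions, self-monitoring, review of homework". Phase 2 also has a weekly element: "The usability evaluation by youth will be done via a short weekly interview conducted upon arrival at the therapy session". Its satisfaction ratings cover most of the same topics but not review of homework.

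**The concern.** A mediator has to precede the outcome that it is said to transmit an effect to. If the rating is given after the posttreatment assessment, and in retrospect, a youth who feels better can attribute more support to the app. Rating and outcome are then correlated at a given level of homework, even if support did nothing. A path model fitted to these data cannot tell that correlation from mediation.

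What is at stake is a statement about mechanism. The analysis runs only when the app group has done better, which is when such a statement is most likely to be reported.

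**Working it through.** The plan states no figure for this analysis, so there is none to reproduce. The check has two parts: the order of measurement, and how much bias that order could produce.

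**Order of measurement**

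1. Predictor: homework, weekly during treatment (Phase 3, Measures).
2. Posttreatment outcomes: end of the 12 weeks (Phase 3, Study Design and Measures).
3. Mediator: the six-item list includes review of homework. Among the Phase 2 rating lists, only the final interview has that item. Phase 3, Measures puts the usability evaluation after the posttreatment assessment.
4. Follow-up outcomes: 6 and 12 months later.

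So the mediator follows the posttreatment outcome and precedes the follow-up outcomes. For the follow-ups the order is nominally right, but the rating may already reflect improvement that persists.

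**Possible size.** Every coefficient below is an assumption; the documents give none. Variables are standardised, support has no effect on outcome, and mediation is declared when both paths have p < .05.

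*Model A, reverse effect only.* Homework correlates c with improvement, and improvement correlates r with the rating. Then a = rc, b = r(1 − c²)/(1 − r²c²), and

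ab = r²c(1 − c²)/(1 − r²c²).

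- c = 0.3, r = 0.3: 0.09 × 0.3 × 0.91 / 0.9919 = 0.025, which is 8% of the total effect 0.3.
- c = 0.3, r = 0.5: 0.25 × 0.3 × 0.91 / 0.9775 = 0.070 (23%).
- c = 0.5, r = 0.3: 0.09 × 0.5 × 0.75 / 0.9775 = 0.035 (7%).
- c = 0.5, r = 0.5: 0.25 × 0.5 × 0.75 / 0.9375 = 0.100 (20%).

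These are large-sample values, so the bias is not a small-sample artefact. Over r and c from 0.3 to 0.5, simulated false-positive rates were 3–23% with 35 youth and 5–40% with 50, against 0.1–0.3% when r = 0. (The article uses 35 per group for power and recruits 10 × 5 = 50.) For a later outcome correlated 0.6 with posttreatment status, ab is 0.6 times as large and the rates were 1–17%.

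*Model B, homework also raises the rating directly.* There are 45 youth (50 less 10%). Homework to symptoms is −0.30 and the pretreatment value, used as a covariate, has coefficient 0.5. Residual outcome variance is 1 − 0.09 − 0.25 = 0.66. The rating has variance 1, homework-to-rating path h and reverse coefficient k. Then a = h + 0.3k, v = 1 − (h² + k² + 0.6hk), and b = −0.66k/(0.66k² + v).

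| h | k | a | b | ab | Declared present |
|---|---|---|---|---|---|
| 0.3 | 0 | 0.30 | 0 | 0 | about 2.5% |
| 0.3 | 0.3 | 0.39 | −0.240 | −0.09 | 32% |
| 0.3 | 0.5 | 0.45 | −0.449 | −0.20 | 82% |
| 0 | 0.3 | 0.09 | −0.204 | −0.02 | about 3% |
| 0 | 0.5 | 0.15 | −0.361 | −0.05 | about 13% |

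With no reverse effect and h = 0, both paths must be falsely significant: 0.05 × 0.05 = 0.25%. That is the benchmark for the two bottom rows. If the rating's residual variance is fixed at 1, the 32% and 82% fall to about 23% and 53%.

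For a follow-up outcome with h = 0.3, adjusting for the pretreatment value alone gave 12% (k = 0.3) and 33% (k = 0.5). Adding the posttreatment value gave 2.5% and 3.4%.

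**The case against.** **The source of the ratings is not beyond doubt.** The Phase 3 evaluation reuses the Phase 2 protocol, which contains weekly interviews, and two items in the mediator list are worded as in the weekly ratings. This stands as an ambiguity. Phase 3, Measures still places the evaluation at posttreatment, and review of homework is missing from the weekly list. If weekly ratings were meant, the text should say so.

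**The model is not fully specified in the article.** A reader might infer that the follow-up mediation is adjusted for the pretreatment value only. The documents do not support that: the pretreatment control belongs to the preceding paragraph, on regressions of outcome on homework. The mediation paragraph names no covariates, and an article may leave them to a fuller document. What stands is that posttreatment outcomes are not excluded and the stated timing of the ratings does not suit them.

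**The large rates are fragile.** A reader might take 82% as the expected error rate. It depends on a direct homework-to-rating path of 0.30 as well as on the reverse effect; without that path the figure is about 13%. The direction of the bias stands; its size does not.

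**Little depends on the result.** A reader might infer that app features would be kept or dropped on this analysis. The article says no such thing: under Usability Evaluation, improvement of the app rests on the usability data. The analysis is exploratory and conditional. This stands and lowers the weight of the point, but exploratory status does not repair the order of measurement.

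**The chain itself is open to question.** The section The Role of Mobile Tools expects support for learning to improve homework, the reverse of the mediation paragraph. That is a separate matter: drawn either way, the rating still follows the posttreatment outcome.

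**Conclusion.** The point holds as a minor one. On the most natural reading of the Phase 2 Procedure and Phase 3 Measures sections, the mediator is rated once, after the posttreatment outcomes are recorded. An indirect effect on those outcomes could not be read as mediation. Follow-up outcomes are measured after the rating but can carry some of the same bias through improvement already reached.

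The size cannot be known from the documents. With no true effect of support, false-positive rates for the posttreatment outcome ran from about 3% to over 80%, depending on the assumed reverse effect and the assumed homework-to-rating path. The conclusion rests on the ratings coming from the final interview and on improvement colouring them to some degree. The primary homework comparison and the group comparisons of outcomes are unaffected.

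**What to change.** In Phase 3, Measures, have the app group give the six support ratings at an already scheduled session during treatment, before the posttreatment assessment. In the mediation paragraph, use homework from the weeks before that rating as the predictor. For example, a rating after the middle block of homework weeks would leave 4 + 4 = 8 of the 11 analysed weeks. The cost is one short rating set and less homework data in the model. Early improvement could still colour the rating to some degree, and no symptom measure is planned at that time to adjust for it.

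If the ratings stay where they are, state that the posttreatment result will be reported as an association and not as mediation. This costs one sentence.

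A follow-up analysis adjusted for both the pretreatment and the posttreatment value may be added as a sensitivity analysis. It should carry a note that it addresses only change after posttreatment: it removes the improvement reached during treatment, and so answers a narrower question.
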